### Statistical analysis

The main analytical aims of the study are to measure the demographics of the cohort and to estimate the recruitment, compliance and retention rates, to use as a basis of the design and sample size determination of future studies. Analysis of the screening log will provide data regarding the number of potential eligible patients recruited and the reasons for non-recruitment. The number of withdrawals and reasons for withdrawals will be assessed. Patient demographics will be summarised using rates, means and standard deviations or medians and ranges/interquartile ranges, as applicable.

The data collected will also be used to perform a preliminary analysis, to identify whether any of the clinical or patient-reported endpoints differ between the two treatment groups. Baseline and demographic factors will initially be compared between the two groups, in order to ensure balance. Withdrawal rates will also be compared, in order to ensure that those patients in the enhanced rehabilitation group are not at a higher risk of leaving the study. Outcome measures will then be described for each group separately to assess whether change over time can be observed in order to identify potential target outcome measures to utilise in future studies. Effect sizes will be reported as estimates with 95% confidence intervals and without *p* values, as the trial is not powered for testing hypotheses about effectiveness.

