### Aims and objectives

The aim of this feasibility study is to inform the design of a future multicentre phase III randomised controlled trial of enhanced rehabilitation compared to standard care in patients mechanically ventilated for 5 days or more. This time point has been specifically chosen to target a patient cohort at greatest risk for ICUAW and persistent critical illness [25, 27]. Specifically, the objectives are to:Estimate rates of recruitment and consent from eligible patients and to describe the baseline characteristics of the participants in terms of co-morbidities, physical function and illness severity.Test the rehabilitation intervention in terms of compliance, differentiation from standard care and ability to increase mobility levels at ICU discharge.Estimate retention of participants and response rates to follow-up questionnaires.Evaluate a range of clinical and patient-reported outcome measures to aid selection of the most appropriate primary outcome measure for a definitive trial, with estimates of variance for sample size calculation.

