#### Data collection

At recruitment, demographic data including age, sex, reason for ICU admission, illness severity score (APACHE II) [29] and the Charlson co-morbidity score [30] will be recorded, and retrospective estimates of the Barthel [31] and Short Form-36 scores [32] will be taken from family members. Daily data will be collected until discharge from the ICU on SOFA score, sedation use, delirium and nutritional intake.

All medical care will be at the discretion of the responsible intensivist. Rehabilitation interventions by all members of the clinical team at each stage of the patient pathway will be carefully recorded, with analysis of the reasons for missed rehabilitation sessions performed. In accordance with current unit practice, all patients with a length of stay over 14 days will be discussed at weekly multidisciplinary team meetings which include consultant medical staff, senior nursing staff, speech and language therapists and occupational therapists, with collaborative treatment goals set, reviewed and updated.

Participants will have muscle thickness of quadriceps and biceps measured on recruitment and ICU discharge using ultrasound. Blood will be drawn between 8 am and 10 am on recruitment and weekly until hospital discharge or 6 weeks (whichever is the sooner) for 25-hydroxy vitamin D (all patients) and for cortisol, dehydroepiandrosterone-sulphate (DHEAS) and cortisol metabolites (all patients not receiving steroids as part of their medical management). A subset of patients will also have blood taken at recruitment, week 1 and week 2 for cytokine and neutrophil function. This is to provide exploratory data about the potential impact of rehabilitation on muscle thickness and immune-endocrine function in chronic critical illness.

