### Outcome measures

This study will evaluate the feasibility of the enhanced rehabilitation intervention in terms of recruitment process, compliance and differentiation from standard care and provide pilot data as to outcome measures and variance for a phase III trial. For the recruitment process, this will be the proportion of eligible patients who are recruited and then complete all study assessments. Within a single centre, there is a significant risk of changing practice within the control group over the course of the study. Compliance and differentiation of groups will be assessed by process measures such as the daily maximum MMS achieved compared to the level of organ support required, time to first mobilisation (defined as sitting on the edge of the bed (MMS ≥ 2)), proportion of patients who have weekly goals set and documented treatment plans, dose of physiotherapy in terms of therapy time, recording of reasons for missed sessions and mobility level at ICU discharge.

Outcome measures to be evaluated for potential use within a definitive trial are as follows:ICU and hospital length of stay and mortality, as enhanced rehabilitation has been shown to be associated with reduced length of stays and mortality in published literature [16, 17].Medical Research Council (MRC) sum score and hand grip strength as a measure of ICU-acquired weakness [33].Functional status as assessed by the Barthel index score at ICU and hospital discharge, 3 and 12 months [31].Health-related quality of life as assessed by SF-36 at ICU and hospital discharge, 3 and 12 months [32, 34].Anxiety and depression as assessed by the Hospital Anxiety and Depression Scale score at ICU and hospital discharge [35, 36].

Completion of the Barthel, SF-36 and HADS scores will be co-ordinated by the research nursing team. Three- and twelve-month assessments will be via telephone interview, with a follow-up sent by post if no response is received. NHS records will be accessed by the nursing team to ensure that no deceased patients are contacted.

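### A baseline comparison cannot ensure balance, and no baseline-adjusted estimate is stated for the measures that have a baseline value

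*Protocol article*

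**What the plan says.** All references are to the protocol article.

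- **Baseline (Statistical analysis).** "Baseline and demographic factors will initially be compared between the two groups, in order to ensure balance".
- **Outcomes (same section).** "Outcome measures will then be described for each group separately to assess whether change over time can be observed". The section then says: "Effect sizes will be reported as estimates with 95% confidence intervals and without" p values. It does not say whether these estimates are adjusted or unadjusted.
- **Use of the results (Aims and objectives).** The candidate outcomes are to be evaluated "with estimates of variance for sample size calculation". The Discussion repeats this purpose.
- **Baseline values collected.** In Data collection, "retrospective estimates of the Barthel [31] and Short Form-36 scores [32] will be taken from family members", and "Participants will have muscle thickness of quadriceps and biceps measured on recruitment and ICU discharge using ultrasound". Table 3 also schedules MMS at allocation.
- **Baseline values not collected.** Outcome measures lists "Anxiety and depression as assessed by the Hospital Anxiety and Depression Scale score at ICU and hospital discharge", so HADS has no baseline. In Table 3 the MRC sum score and grip strength begin weekly during the ICU stay, with no entry at allocation. Length of stay and mortality cannot have a baseline value.
- **Stratification (Randomisation and blinding).** Age (below 50 or not) and SOFA score (below 9 or not).

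**The concern.** Randomisation makes the arms comparable in expectation. Among all randomised patients, a later baseline difference is chance. Looking at that difference does not remove it from an arm contrast, and seeing none does not protect the contrast. The stated purpose of the comparison is therefore one it cannot serve.

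This matters more here than in a large trial. The study expects about 100 patients and high mortality, and it stratifies only on age and SOFA, so pre-morbid function is left to chance. The Background itself faults recent trials of early rehabilitation for baseline differences between groups.

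Two reported quantities are affected: the effect estimates with their confidence intervals, and the variance offered to phase III. If phase III adjusts for baseline, the variance it needs is the residual one. That cannot be recovered from a raw SD unless the baseline-outcome correlation is reported too.

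**Working it through.** The article gives no sample size calculation, SD or power, so there is no figure of its own to reproduce.

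**Inputs from the article (Sample size).** About 100 patients; in-hospital mortality of up to 30%.

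**Assumptions.** 1:1 allocation, so 50 per arm and 50 × 0.70 = 35 survivors per arm before other losses. The baseline-outcome correlation r is not given; 0.2 to 0.7 is shown. Normal quantiles are used, and the one degree of freedom spent on the covariate is ignored.

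**Step 1: chance imbalance.** The SD of a between-arm baseline difference is √(2/n), in baseline SD units.

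- n = 50: √(2/50) = 0.200; the probability of a difference above 0.2 SD in either direction is 0.32.
- n = 35: √(2/35) = 0.239; that probability is 0.40.

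The second line treats survivors as if they were a randomised set. Survival comes after randomisation, so imbalance among survivors need not be pure chance; the figure is a guide only.

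**Step 2: effect on an unadjusted estimate.** The shift is r × imbalance. The typical shift uses an imbalance of 0.239 SD; the 95% extreme uses 1.96 × 0.239 = 0.469 SD.

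**Step 3: precision and variance.** Unadjusted CI half-width is 1.96 × √(2/35) = 0.469 SD. Adjusted half-width is 0.469 × √(1 − r²). The variance falls by r².

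| r | Typical shift (SD) | 95% extreme shift (SD) | Adjusted half-width (SD) | Fall in variance |
|---|---|---|---|---|
| 0.2 | 0.05 | 0.09 | 0.46 | 4% |
| 0.3 | 0.07 | 0.14 | 0.45 | 9% |
| 0.5 | 0.12 | 0.23 | 0.41 | 25% |
| 0.7 | 0.17 | 0.33 | 0.33 | 49% |

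With 50 per arm the unadjusted half-width is 0.392 SD, and the adjusted values are 0.384, 0.374, 0.339 and 0.280 SD.

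**Step 4: what this means for phase III.** As an illustration only, take an assumed difference of 0.3 raw SD, two-sided 5% significance and 80% power. The total N is 350 on the raw SD, and 336, 318, 262 or 178 on the residual SD at r = 0.2, 0.3, 0.5 or 0.7.

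**Step 5: which measures this reaches.** Barthel, SF-36, MMS and muscle thickness have their own baseline value. Only Barthel and SF-36 are on the list of candidate phase III outcomes. MMS is a process measure, and muscle thickness is exploratory.

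**The case against.** Several stronger readings are tempting, and the article does not support them.

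- **That the plan rejects adjustment.** A reader might infer that the balance check replaces adjustment, or that adjustment will be chosen after seeing the data. Neither is stated. The article names no model, and the choice of covariates is commonly left to a full protocol or SAP that is not shown. The silence alone is no finding.
- **That the estimates will be biased.** Randomisation keeps an unadjusted contrast unbiased on average, with a valid interval.
- **That the raw SD is wrong for phase III.** It is conservative if phase III adjusts, and right if it does not.
- **That each SD will rest on half the patients.** "Outcome measures will then be described for each group separately" is there to show change over time. Nothing forbids pooling, and two arm SDs can be pooled directly.
- **That every outcome can be adjusted for its own baseline.** Length of stay, mortality, HADS, MRC sum score and grip strength cannot.

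It can also be said that the word ensure is loose usage for check: the next sentence, on withdrawal rates, uses it in that sense. This is fair, and no baseline significance test is mentioned. Even so, a check does nothing for the estimates, and it is the only handling of baseline differences that the section states.

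The strongest objection concerns size. Baseline Barthel and SF-36 are family members' recollections of pre-illness status, while follow-up at 3 and 12 months is by telephone or post. Their correlation with outcome could be weak; at 0.1 to 0.2 the fall in variance is only 1% to 4%. MMS at allocation may also vary little, since most patients then have altered consciousness. This stands, and it is why the low correlations belong in the range.

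**Conclusion.** The point holds in limited form. The stated purpose of the baseline comparison is mistaken, and the article states no baseline-adjusted estimate for the four measures whose baseline it collects. The loss is precision and imbalance within this sample. It is negligible if the correlation is 0.2 or less and material from about 0.5 upward: a 25% fall in variance at 0.5 and 49% at 0.7. These sizes rest on 1:1 allocation, about 35 survivors per arm treated as a randomised set, and an assumed correlation.

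Recruitment, compliance, retention and differentiation of therapy dose, on which the study is to be judged, do not depend on this. It is a modest, inexpensive improvement that serves the stated aim of supplying variance estimates.

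**What to change.** 1. Delete the closing clause of the baseline sentence, on ensuring balance, and say that baseline characteristics will be tabulated by arm descriptively.
2. Add, for example: *Arm differences in Barthel, SF-36, MMS and muscle thickness will be estimated by regression on arm and the baseline value of that measure, whatever balance is observed.*
3. Report for each of these measures the raw pooled SD, the residual SD and the baseline-outcome correlation, so that phase III can choose between an adjusted and an unadjusted design.

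The cost is a change of wording and one regression per measure, with no new data. Patients without a baseline value would need simple imputation or a missing indicator. The gain may prove small if the family-reported baselines correlate weakly with outcome, but the reported correlation would then show that.

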### Adverse event management

An adverse event is defined as any untoward medical occurrence in a subject and which does not necessarily have a causal relationship with this treatment. A serious adverse event (SAE) is an adverse event that fulfils one or more of the following criteria:Results in deathIs immediately life-threateningRequires prolongation of existing hospitalisationResults in persistent or significant disability or incapacityIs an important medical condition

Serious adverse events will be reviewed by the study team, and likely causality will be assessed and recorded on the SAE form. All SAEs will be notified to the sponsor’s research and development department via the SAE form in the CRF. Only those events classified as probable or definitely related will be reported to the Research Ethics Committee. Because this study is recruiting a population that is already in a life-threatening situation, it is expected that there will be a high rate of SAEs.

## Discussion

Optimising the recovery of survivors of critical illness is an important area of research that has been highlighted as a priority by the intensive care community. Early and enhanced rehabilitation on the ICU has been shown to be safe [37] and to be associated with short-term improvements in clinical outcomes in some studies. Our findings will determine whether recruitment to a full-scale trial of enhanced rehabilitation of mechanically ventilated patients is feasible. They will allow detailed information on the delivery and dose of the intervention to be collected, allowing refinement if necessary. Success of this feasibility study will be judged by whether it is possible to show that a differentiation in dose of therapy between groups is achievable and measurable. Whilst this study is not powered to detect clinically important differences in patient outcomes, it will provide important information about the trajectory of recovery from critical illness and enable sample size calculations to be performed for the design of a phase III trial. A dissemination plan which includes conference presentations and publication in open access peer-reviewed journals following the extended CONSORT principles [38] is in place.

## Trial status

The trial is open and recruiting.

## Abbreviations

CRF: Case report form
DHEAS: Dehydroepiandrosterone-sulphate
ICU: Intensive care unit
MMS: Manchester Mobility Score
QEHB: Queen Elizabeth Hospital Birmingham
SOFA: Sequential Organ Failure Assessment score
